**Objective:**

This paper presents the protocol for the DREAMPath (Domiciliary Recovery After Medicalization Pathway) study, which aims to measure compliance with a multidevice remote monitoring kit after discharge from hospital following major surgery.

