### Study Period

Patients will provide consent either prior to having surgery or in the immediate postoperative period while they are still in hospital. At the time of consent, patients will be familiarized with the smart devices and mobile app described. If the patients undergo cardiopulmonary exercise testing (CPET) as part of their routine assessment, the results for this will be recorded. This data will be used to compare the performance of CPET data and smart device data in predicting postoperative complications.

The 4-week monitoring period will commence upon discharge from hospital. Patients will be expected to wear the wearable device at all times, engage with other devices (see the *Remote Monitoring Equipment* section below for the list of devices) twice a day, and fill out 1 daily questionnaire. Compliance will be defined as completion of 70% of the daily PROM questionnaires or wearing the wrist-worn trackers for at least 10 hours per day over the study duration. A minimum of 1 reading in each hour of either step count or heart rate will constitute a successful hour of data collection. Patients will be given the opportunity to contact dedicated personnel in the study team for troubleshooting purposes only. Furthermore, the app provides clear feedback to patients to signal the successful collection of study data. We hope that this measure will help patients feel supported to engage with the study and reduce patient withdrawal. If patients are admitted to the hospital during the monitoring period, they will not be expected to bring the HALO kit to the hospital, and the admission period and subsequent use will not factor into their compliance rate.

The end of the study will be defined as completion of a 30-day follow-up after discharge from the hospital. Patients will be seen at the clinic or contacted by phone to conclude their participation. Postdischarge events will be collected at this time, which is defined as any unscheduled contact with a health care professional, which includes, but is not limited to, general practitioner (GP) visits, accident and emergency (A&E) visits, home visits by primary care team, etc.

All study assessments are summarized in Table 1, and the study flowchart is illustrated in Figure 1. As DREAMPath is an observational study, patients will be able to participate in other trials.

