### Remote Monitoring Equipment

The HALO kit is designed to be used with a cellular broadband device, such as a 4G-capable mobile phone, which can be used to complete questionnaires electronically. The broadband device remotely uploads data to an anonymized database. Patients will be issued a HALO kit before discharge from hospital and will be monitored remotely for 30 days. The HALO kit consists of 4 devices: a wrist-worn device with step count and heart rate measurement capability, an iHealth Air pulse oximeter, an iHealth Track blood pressure monitor, and a Koogeek Thermometer. These devices are shown in Figure 2. Patients without a smartphone will be provided with one for the duration of the study. Patients will be instructed to wear the tracker continuously and will be shown how to measure blood pressure, pulse oximetry, and temperature twice daily (morning and evening). All readings will be transmitted from the respective device to the iPhone wirelessly, with the option for patients to self-enter data if they prefer to. Additionally, they will be asked to complete a QoR-15 questionnaire once daily.

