### Conclusion

Health care services have undergone a digital revolution during the COVID-19 pandemic. Hospitals were routinely giving patients medical devices to self-monitor, and this initiative was supported by national organizations such as NHS England [21]. This is based on evidence that the prehospital measurements of pulse oximetry can be a red flag for patients who may be experiencing “silent hypoxia” due to COVID-19 infection. However, these devices did not have any way of interacting directly with hospital systems and patients were asked to maintain a diary of readings, which can be reviewed by clinicians via remote consultation or A&E attendances. Our study was conceived prior to the pandemic, but offers an important improvement to the current pathway as patients do not need to enter any data manually as the devices included sync data directly using Bluetooth and our bespoke app allows for an automatic upload. After the completion of this study, we hope to integrate our backend server to communicate directly with hospital electronic health record systems to allow seamless data access for clinicians while patients are at home.

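### The either/or compliance rule gives three of the four HALO devices no role, so the primary outcome does not measure the kit compliance on which the feasibility conclusion rests

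*Protocol article*

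**What the plan says.** The Objective paragraph of the abstract says the study "aims to measure compliance with a multidevice remote monitoring kit after discharge from hospital following major surgery". Study Design repeats that the HALO kit is the object of the compliance assessment. The Primary Objective names wearable and interactive technology together, and the end of the Introduction gives the overarching aim as the feasibility of collecting physiological data together with patient-reported outcomes.

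Remote Monitoring Equipment lists the contents: "The HALO kit consists of 4 devices: a wrist-worn device with step count and heart rate measurement capability, an iHealth Air pulse oximeter", followed by a blood pressure monitor and a thermometer. Study Period asks three things of patients: constant wear of the tracker, use of the other devices twice a day, and one questionnaire a day.

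The same section then sets the rule: "Compliance will be defined as completion of 70% of the daily PROM questionnaires or wearing the wrist-worn trackers". The second route is specified as "wearing the wrist-worn trackers for at least 10 hours per day over the study duration". An hour of wear is judged as follows: "A minimum of 1 reading in each hour of either step count or heart rate will constitute a successful hour of data collection".

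Power Calculation anticipates one per-patient count, 27 of 30 (90%). Strengths and Limitations says that the primary outcome will show whether remote monitoring is feasible.

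**The concern.** The aims join their parts with 'and'; the rule joins two of them with 'or' and leaves out the rest. The three devices it omits supply blood pressure, oxygen saturation and temperature. Those readings are central to the early-warning work described under Benefits of the Study, for which measured engagement is meant to be the preparatory step.

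A high compliance figure under this rule would show that most patients did at least one of two things. It would not show that they used the kit. A reader planning a larger study could take 90% as the rate at which patients supply the full set of measurements, which the rule cannot establish.

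**Working it through.** **The plan's own figure.** Power Calculation gives 82% as the exact one-sided 90% lower limit for 27/30. The Clopper-Pearson limit is the 10% quantile of Beta(27, 4), which is 79.1%. As a check, P(X ≥ 27) at p = 0.82 with n = 30 is 0.186, where 0.10 is needed. The 82% does not reproduce. That is a separate matter and nothing below depends on it. What matters here is that the anticipation is a single yes/no count per patient.

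**What each route requires.**

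| Task asked of patients | Role in the compliance rule |
|---|---|
| Daily questionnaire | Route 1: 70% completed |
| Wrist tracker | Route 2: at least 10 h/day; steps alone suffice for an hour |
| Pulse oximeter, twice daily | None |
| Blood pressure monitor, twice daily | None |
| Thermometer, twice daily | None |

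- Route 1 alone: 0.70 × 28 = 19.6, so 20 questionnaires; or 0.70 × 30 = 21. Both are shown because Study Period describes a 4-week monitoring period and a 30-day follow-up. No reading from any device is needed.
- Route 2 alone: 10 hours a day of step counts. No heart rate, blood pressure, oxygen saturation or temperature is needed.

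So 30/30 compliant is logically possible with no vital sign recorded.

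**How far the either/or rate can sit from the rate for both.** Let q and t be the proportions meeting routes 1 and 2. The document gives neither. Then

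both = q + t − either.

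Fix either = 0.90, the anticipated rate.

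- Bounds: q and t are each at most 0.90 and sum to at least 0.90. So both runs from 0.90 − 0.90 = 0% to 0.90 + 0.90 − 0.90 = 90%, that is 0 to 27 of 30 patients.
- Independent with equal rates p (assumption): 1 − (1 − p)² = 0.90, so p = 1 − √0.10 = 0.684 and both = p² = 0.468, about 14 of 30. The exact one-sided 90% lower limit for 14/30 is 33.8%.
- Independent with unequal rates (assumption): 50% and 80% give either = 1 − 0.5 × 0.2 = 90% and both = 40%; 60% and 75% give either = 1 − 0.4 × 0.25 = 90% and both = 45%.
- Equal rates with correlation 0.5 (assumption): both = p² + 0.5p(1 − p), so either = 1.5p − 0.5p² = 0.90. This gives p = 1.5 − √0.45 = 0.829 and both = 2 × 0.829 − 0.90 = 0.758, about 23 of 30.

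**The other three devices.** They do not enter the rule, so any either/or rate is compatible with 0% to 100% using them as asked.

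**The case against.** - **'Or' could mean two separately reported measures.** The single 27 of 30 count fits one combined endpoint better. On either reading the three devices are still left out.
- **The Primary Objective can be read as tracker (wearable) plus phone questionnaire (interactive).** This is fair, and the rule then touches both named parts. But that objective asks for both and the rule accepts either, while the abstract and Study Design speak of the kit.
- **The extreme case is unlikely.** Exclusion Criteria remove patients unable or unwilling to comply with monitoring, a telephone call confirms activation, and the app signals successful collection. This stands. A reader might infer that the study is likely to declare feasibility with no vital signs. The documents show only that the rule permits it, and the secondary analyses would still use whatever readings arrive.
- **Engaged patients tend to do both tasks.** Also fair: dependence narrows the gap, as the correlation of 0.5 shows. No single value for the rate of meeting both should be presented as expected.
- **Self-entry.** A reader might see a contradiction between readings sent "with the option for patients to self-enter data if they prefer to" and the Conclusion's statement that "patients do not need to enter any data manually as the devices included sync data directly using Bluetooth". There is none: something can be optional and also not needed. It has no bearing on the either/or rule and gives no reason to discount self-entered readings.
- **A lenient rule suits a 30-patient feasibility study with no formal go/no-go threshold.** A lenient threshold is defensible. Leaving most of the kit out of an outcome about the kit is a different matter. Nor is this detail that an article may leave to an analysis plan, since the article states the definition outright.

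**Conclusion.** The point holds as a mismatch between the primary outcome and the aims it serves. That rests on the text alone. Its size depends on component rates that the article does not give: at 90% under the either/or rule, the illustrations above run from 40% to about 76% meeting both, within logical bounds of 0% to 90%.

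A reader might go further and conclude that compliance must be redefined as meeting every component. The documents do not require that. A strict all-parts rule is debatable, and it would remove the basis of the 27 of 30 anticipation. What is needed is that the either/or figure is not presented as kit compliance and that feasibility is judged on what was actually measured.

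**What to change.** 1. Keep the either/or rule only under a name that describes it, such as 'at least one component'.
2. Report, each with an exact confidence interval, the proportion of patients meeting the questionnaire rule, the tracker rule, both, and a prespecified share of scheduled readings for each of the three twice-daily devices. The same 70% would be one option: 0.70 × 56 = 39.2, so 40 readings per device over 28 days, or 0.70 × 60 = 42 over 30 days, for a patient with no readmission.
3. Base the feasibility conclusion on these component rates.
4. State in Power Calculation that 27 of 30 refers to the either/or rule.
5. To make the tracker rate and the rate for both computable, say whether 10 hours per day means every day, an average or a share of days, and whether the period is 28 or 30 days.

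The cost is some wording and a few table rows, using readings that the study already collects. Because the study is under way, the change should be documented before the compliance data are analysed. The real downside is that the figures supporting feasibility will probably be lower than a single either/or rate.

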## Methods

### Study Design

This is a prospective, single-center, observational study to assess patient compliance with smart technology devices using the Home and Locally Observed (HALO) kit. The study will recruit patients undergoing any major intracavity surgery, which is associated with a readmission rate of >15% within 30 days of surgery or >20% in the first 90 days of surgery.

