### Objectives

#### Primary Objective

The primary objective of the study is to assess patient compliance with wearable and interactive smart technology in the 30 days following discharge from hospital after major intracavity surgery.

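### Readmitted patients are scored for compliance only up to readmission, which conflicts with the 30-day primary objective; the documents do not fix the direction of the bias

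*Protocol article*

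**What the plan says.** All places are in the protocol article.

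- **Study Period**, on scoring patients admitted during monitoring: "the admission period and subsequent use will not factor into their compliance rate".
- **Study Period**, the reason offered for that rule: "they will not be expected to bring the HALO kit to the hospital".
- **Study Period**, definition of compliance: "completion of 70% of the daily PROM questionnaires or wearing the wrist-worn trackers for at least 10 hours per day over the study duration".
- **Primary Objective**: to "assess patient compliance with wearable and interactive smart technology in the 30 days following discharge".
- **Remote Monitoring Equipment**: patients "will be monitored remotely for 30 days".
- **Study Design**: eligible operations are those "associated with a readmission rate of >15% within 30 days of surgery or >20% in the first 90 days of surgery".
- **Power Calculation**: 30 patients, with 27 (90%) expected to comply. Each patient counts as one compliant or non-compliant unit.

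The article states no minimum number of evaluable days for a patient whose window is cut short.

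**The concern.** Leaving out inpatient days is reasonable, because the kit is not expected to go to hospital. That is the only reason given, and it does not extend to home days after the patient has been discharged again. Dropping those days means that a readmitted patient who then abandons the kit cannot be scored non-compliant for doing so, and one who resumes it well gets no credit.

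The operations are selected for a high readmission rate, so the rule will be used. It also falls on the patients who matter most to the study's question: the abstract describes the group as at raised risk of acute deterioration, and Strengths and Limitations says the primary outcome will show whether remote monitoring is feasible. For these patients the primary outcome would not be the quantity that the objective names.

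**Working it through.** **1. The passages side by side.** The definition runs over the study duration, and the objective and the equipment section both give 30 days. (Study Period also speaks of a 4-week period; 30 days is used here.) The readmission rule replaces that window with discharge to readmission. Two patients readmitted on days 3 and 20 are measured over 3 and 20 days, and each enters the cohort rate with the same weight as a patient observed for 30 days.

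**2. The plan's own figure.** The exact one-sided 90% lower limit L for 27/30 solves P(X ≥ 27 | n = 30, L) = 0.10, so L is the 0.10 quantile of Beta(27, 4) = 0.791. Power Calculation states 82%, but P(X ≥ 27 | 0.82) = 0.186, not 0.10. The exact one-sided 80% limit is 82.4%. This mismatch is a separate matter and does not bear on the present point; 79.1% is used below.

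**3. How many patients.** 30 × 0.15 = 4.5, so about 4 to 5. The 20% rate gives 30 × 0.20 = 6, but over 90 days. Both rates count from surgery while the monitoring window starts at discharge, so they are only rough guides.

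**4. Effect of changed classifications.** One patient is 1/30 = 3.3 points. The limit for x/30 is the 0.10 quantile of Beta(x, 31 − x).

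| Compliant | Rate | Exact one-sided 90% lower limit |
|---|---|---|
| 27/30 | 90.0% | 79.1% |
| 26/30 | 86.7% | 75.1% |
| 25/30 | 83.3% | 71.3% |
| 24/30 | 80.0% | 67.5% |
| 23/30 | 76.7% | 63.9% |
| 22/30 | 73.3% | 60.3% |

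The last two rows require all 4 or all 5 readmitted patients to pass before readmission and to fail over all home days.

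**5. Is a short window easier to pass?** On the questionnaire criterion, 3 days need 3 of 3 (0.7 × 3 = 2.1, rounded up), 10 days need 7, and 30 days need 21. Binomial chance of passing at a constant daily completion rate:

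| Daily rate | 3 days | 10 days | 30 days |
|---|---|---|---|
| 0.6 | 0.22 | 0.38 | 0.18 |
| 0.8 | 0.51 | 0.88 | 0.94 |

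For example, 0.8³ = 0.512. Truncation helps weak users and hurts good ones.

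**6. Present rule against all home days.** The article gives no daily compliance, no trend over time and no readmission timing, so the patterns below are assumptions. The simulation used a 30-day window, a 4-day admission, readmission after 10 days unless stated, and the questionnaire criterion only. With 10 days before readmission there are 26 home days, so 19 questionnaires are needed (0.7 × 26 = 18.2).

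| Assumed daily completion | Pre-readmission days only | All home days | Direction |
|---|---|---|---|
| Falls from 0.95 to 0.60 | 0.99 | 0.77 | upward |
| 0.9 before, 0.5 after readmission | 0.99 | 0.25 | upward |
| Constant 0.8 | 0.88 | 0.87 | neutral |
| Constant 0.8, readmitted after 5 days | 0.74 | 0.87 | downward |
| 0.9, but 0.4 in the last 3 days before readmission | 0.81 | 0.97 | downward |
| Rises from 0.6 to 0.9 | 0.50 | 0.71 | downward |

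A hand check of the second row: 10 × 0.9 + 16 × 0.5 = 17 expected questionnaires, below the 19 needed, whereas 9 of 10 are expected before readmission.

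**The case against.** The strongest defence is that use up to the first readmission is a legitimate target. The kit is meant to help predict an unplanned event, so use before that event is the relevant exposure. This fits the secondary, predictive objective. It does not fit the primary one, which is compliance over 30 days after discharge with no reference to a first event.

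A second defence is that this is a 30-patient feasibility study with no test and no stated go/no-go threshold, and that minimum evaluable days and sensitivity analyses commonly sit in an analysis plan. That limits how much rests on the point. It does not remove it, because the article states the exclusion as a rule and does not leave it open. If only use in hospital was meant to be excluded, the sentence does not say so.

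Three further objections stand:

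- A reader might infer that the rule inflates compliance. The documents contain nothing on patterns of use, and steps 5 and 6 show that the direction depends on the pattern. Readmission after 3 days demands every questionnaire, which is a stricter bar for a good user.
- Compliance is met by questionnaires or by tracker wear. The calculations cover the questionnaire criterion only. To be reclassified as non-compliant, a patient must fail both over all home days, so changes of status are less likely than the questionnaire figures suggest.
- The article does not say that readmitted patients are expected to resume using the kit. Counting those days fairly requires it to say so.

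**Conclusion.** The point holds as an inconsistency in the primary outcome. For readmitted patients the article measures compliance to readmission and not over 30 days, and it gives no reason for discarding home use after return.

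About 4 to 5 of 30 patients are affected, if the rate counted from surgery carries over roughly to the post-discharge window. Each change of status is worth 3.3 points, and one change from 27/30 moves the exact lower limit from 79.1% to 75.1%.

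The direction is undetermined: upward if use wanes over time or after readmission, neutral or downward if use is steady and good or dips just before readmission. It would be tempting to conclude that 90% compliance is really 73–77%. The documents do not support that. The figure of 22–23/30 is a worst case in which every expected readmitted patient changes status.

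**What to change.** - Exclude only days spent in hospital. Set each patient's denominator to all at-home days from discharge to day 30, including days after re-discharge.
- State that kit use is expected to resume after return home.
- Report the present rule as a sensitivity analysis, with the number of evaluable days for each readmitted patient.

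The cost is a changed sentence on the denominator, a sentence on resumption, and one additional analysis. The downside is that the reported rate may be less favourable. The change should be settled before the data are analysed.

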**Figure 1 figure1:**
[figure not shown]
Flow diagram illustrating visits and assessments for patients participating in the DREAMPath (Domiciliary Recovery After Medicalization Pathway) study. CPET: cardiopulmonary exercise testing; PIS: patient information sheet; POMS: postoperative morbidity score.

### Remote Monitoring Equipment

The HALO kit is designed to be used with a cellular broadband device, such as a 4G-capable mobile phone, which can be used to complete questionnaires electronically. The broadband device remotely uploads data to an anonymized database. Patients will be issued a HALO kit before discharge from hospital and will be monitored remotely for 30 days. The HALO kit consists of 4 devices: a wrist-worn device with step count and heart rate measurement capability, an iHealth Air pulse oximeter, an iHealth Track blood pressure monitor, and a Koogeek Thermometer. These devices are shown in Figure 2. Patients without a smartphone will be provided with one for the duration of the study. Patients will be instructed to wear the tracker continuously and will be shown how to measure blood pressure, pulse oximetry, and temperature twice daily (morning and evening). All readings will be transmitted from the respective device to the iPhone wirelessly, with the option for patients to self-enter data if they prefer to. Additionally, they will be asked to complete a QoR-15 questionnaire once daily.

**Figure 2 figure2:**
[figure not shown]
Smart devices issued to patients for twice-daily use: bluetooth enabled thermometer, puse oximeter, sphygmomanometer, Apple Watch and iPhone 7 (from left to right).

Patients will be registered and provided with a trial identifier to ensure all transmitted data are anonymized. They will be contacted via telephone to confirm activation of the system. At the time of consent, patients will be informed that the data collected will not be reviewed for clinical decision-making and that the data are anonymized. Unplanned health care engagement such as GP visits, A&E visits, and readmissions will be collected as “events.” Postoperative complications will be recorded per the Clavien-Dindo classification and the postoperative morbidity score. An exploratory study to understand whether there is a relation between the measured physical parameters and health care events will be conducted. If a derangement of physiological parameters can reliably predict an unplanned health care engagement event, a similar remote monitoring solution could be used to triage patients at home instead of the current standard of care in which patients self-present to primary or emergency care facilities. Upon completion of the study, patients will be asked to return the devices, and information about unplanned health care events and adverse events will be collected. Patients will not be held responsible for any lost or damaged devices. Study devices will not have any patient-identifiable data; and in the event of a lost device, they will be remotely wiped using Apple’s remote wipe feature on iOS. Upon return, devices will be cleaned and sterilized in line with hospital ambulatory device policy.

